##### Multivariate Analyses

Preliminary outcomes from baseline and 12 week will be tested using repeated measures analysis of covariance, controlling for demographics. EMA data will be tested using multilevel modeling (ie random-coefficient regression model) to examine intervention usability and acceptability, capable of incorporating tests of time-serial characteristics, including linear trend over time and cyclicity. Before multilevel modeling, unconditional means models will be tested for between- and within-participant variation in each measure and determination of appropriate within-person error covariance structure [108].

##### Mixed Method Analysis

Qualitative and quantitative data on feasibility will be triangulated with a complementary proposition [109], in which the qualitative findings will provide in-depth understanding for the quantitative results in terms of intervention feasibility outcomes.

### Power Analysis

The primary aim is to evaluate the feasibility, acceptability, and usability of the intervention to support a future large-scale RCT. According to the guidance for pilot intervention studies [110], it is suggested a minimum sample of 30 per group for the feasibility evaluation. In terms of the aim for the preliminary efficacy evaluation (ie, secondary outcomes of psychosocial and behavioral factors associated with NMUPO), we estimate an effect size according to a previous review on digital interventions for illicit drug use [111] and found small-to-medium effect sizes (Cohen *d*=–0.17 to –0.34) with a 6-month follow-up assessment. G-power analysis [112] estimated a sample size of 10 to 35 per arm for an RCT (repeated measures analysis of covariance). According to previous mHealth trials for substance use with retention rates ranging from 75% to 93% [46,53,61], a sample of 70 appears to be feasible and provides adequate power for proposed analytic plans. Despite a small sample size, this is appropriate for the aim of developmental research.

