Aim 3 involves testing the feasibility and preliminary efficacy of the theory-based social media intervention with a randomized controlled design for NMUPO among young adults. Participants who engage in recent NMUPO will be randomly assigned to 1 of the 2 parallel groups, including the intervention group (35/70, 50%) and control group (35/70, 50%), using a 1:1 allocation ratio. The intervention will be evaluated in terms of feasibility, usability, acceptability, engagement, dose, and preliminary efficacy using mixed methods (eg, surveys, EMA, paradata, and semistructured interviews). During the intervention, EMA (a prompt every 2 days) will assess the acceptability and usability of individual modules. Preliminary efficacy will be tested on behavioral outcomes (ie, past-month NMUPO) and psychosocial factors (eg, outcome expectancy, self-efficacy, action or coping planning, resilience, and psychiatric symptoms).

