## Discussion

### Anticipated Findings

In response to the growing evidence on psychosocial aspects of opioid addiction and relevant disorder concerns in the United States, this proposed study aims to apply a psychosocial theoretical framework and peer role model techniques to develop and implement an evidence-based intervention for reducing NMUPO risk in young US adults. The intervention will be established through a serial research activity, from a formative semistructured in-depth interview study to feasibility evaluation of a 12-week interactive peer-led trial. By leveraging the merits of social media, the proposed intervention study will be powered by adopting innovative approaches, including a tailored recruitment strategy (eg, paid advertisement campaigns), intervention delivery that transcends time and space constraints, and the application of mixed methods and time-series assessments (eg, paradata and EMA measures). As one of the first attempts to deliver peer-led interventions on social media specifically targeting NMUPO, the findings from this mixed methods design will offer valuable insights into the use of innovative approaches for reducing opioid risk among young adults. In line with previous intervention studies for NMUPO on social media [45], we anticipate that our intervention will yield high feasibility outcomes. In particular, the mixed methods assessments for the intervention group will demonstrate (1) high feasibility, acceptability, and usability on all intervention modules among young adults across 12 weeks and (2) high engagement, especially for the modules in the interactive formats, such as discussion polls and live streaming group meetings. We also anticipate significant preliminary intervention efficacy on the NMUPO-related and psychosocial behavior outcomes. Compared to the control group, the intervention will report (1) decreases in past–3-month NMUPO and other substance use (eg, alcohol, illicit drugs, and cigarettes), (2) decreases in psychological distress, (3) changes in outcome expectancies (eg, increased physical discomfort and decreased pain reduction), (4) increases in NMUPO knowledge and NMUPO risk perception, and (5) increases in resilience and self-efficacy (ie, action and coping).

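### The 10 to 35 per arm and the claim of adequate power do not follow from Cohen d of 0.17 to 0.34; the figures are consistent with d having been entered as Cohen's f

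*Protocol article*

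**What the plan says.** All the sample-size reasoning is in the Power Analysis section of the protocol article. Feasibility is the primary aim, and for it "it is suggested a minimum sample of 30 per group for the feasibility evaluation". For the secondary efficacy aim the plan turns to a review of digital interventions for illicit drug use, which "found small-to-medium effect sizes (Cohen *d*=–0.17 to –0.34) with a 6-month follow-up assessment". It then states that "G-power analysis [112] estimated a sample size of 10 to 35 per arm for an RCT (repeated measures analysis of covariance"). After citing retention of 75% to 93% in earlier trials, it concludes that "a sample of 70 appears to be feasible and provides adequate power for proposed analytic plans".

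The analysis being powered is in Multivariate Analyses: "Preliminary outcomes from baseline and 12 week will be tested using repeated measures analysis of covariance, controlling for demographics". Under Aim 3, 70 participants are randomised "using a 1:1 allocation ratio", so 35 per arm. In the Discussion, Anticipated Findings adds: "We also anticipate significant preliminary intervention efficacy on the NMUPO-related and psychosocial behavior outcomes".

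**The concern.** Effects of 0.17 to 0.34 standard deviations are small. Two-arm comparisons of such effects usually need hundreds of participants, so 10 to 35 per arm looks too low by a wide margin. G*Power's repeated-measures routines take Cohen's f, which for a given mean difference is a half or a quarter of d. If d was typed in unconverted, the sample size comes out far too small.

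At stake is the reading of the secondary outcomes. The plan says that the efficacy tests are adequately powered and expects them to be significant. If power is in fact low, a non-significant result says little about the intervention, and a significant one will tend to overstate the effect. The same conversion step, reused for the later full-scale trial, would undersize it.

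**Working it through.** **Inputs from the protocol article.** d = 0.17 to 0.34; 2 groups, 1:1, 35 per arm; 2 measurements (baseline and 12 weeks); retention 75% to 93%.

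**Assumptions (not stated in the document).** Two-sided alpha 0.05, 80% power, pre-post correlation ρ = 0.5. ρ is varied below.

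**1. Reproducing the plan's figure.** For the group-by-time interaction with m = 2 measurements, the noncentrality is λ = f²·N·m/(1−ρ), with 1 and N−2 degrees of freedom.

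| f entered | total N | λ | power |
|---|---|---|---|
| 0.34 | 18 | 8.32 | 0.773 |
| 0.34 | 20 | 9.25 | 0.820 |
| 0.17 | 68 | 7.86 | 0.789 |
| 0.17 | 70 | 8.09 | 0.801 |

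The smallest balanced totals reaching 80% are 20 and 70, that is 10 and 35 per arm. Both ends match when the d values are entered as f.

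**2. What that input implies.** With equal baselines and a week-12 difference of δ SD, the interaction residuals in the four cells are ±δ/4, so f = δ/4. Entering f = 0.17 and 0.34 therefore plans for differences of 4×0.17 = 0.68 SD and 4×0.34 = 1.36 SD, not 0.17 and 0.34.

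**3. Sample size with d converted (ρ = 0.5, 80% power).**

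| Conversion | d=0.34, per arm | d=0.17, per arm |
|---|---|---|
| f = d/2 | 35 | 137 |
| f = d/4 (δ = d) | 137 | 545 |
| baseline-adjusted ANCOVA | about 102 | about 408 |

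The f = d/4 row treats d as a post-treatment difference on the raw SD with equal baselines.

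**4. Could another setting give 10 and 35?** Yes. With f = d/2, (0.34/2)²/(1−0.875) equals 0.34²/(1−0.5), so ρ = 0.875 gives the same λ and the same totals of 20 and 70. With f = d/4, ρ of about 0.97 does so. The document gives no support for either correlation.

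**5. Power at 35 per arm for the stated d.** Noncentral t with effect d/√(2(1−ρ)) for the change score and d/√(1−ρ²) for ANCOVA:

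| ρ | d=0.17: change / ANCOVA | d=0.34: change / ANCOVA |
|---|---|---|
| 0.3 | 9.1% / 11.4% | 22.0% / 31.2% |
| 0.5 | 10.8% / 12.8% | 28.9% / 36.7% |
| 0.7 | 14.8% / 16.6% | 44.1% / 50.1% |

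Reaching 80% by ANCOVA at 35 per arm needs ρ of about 0.87 for d = 0.34 and about 0.97 for d = 0.17.

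**6. Dropout.** 35×0.75 = 26.25 and 35×0.93 = 32.55, so about 26 to 32 per arm remain for the week-12 comparison. At ρ = 0.5, power is then about 9-12% (d = 0.17) and 23-34% (d = 0.34). Having 35 evaluable would mean randomising 35/0.93, rounded up to 38, to 35/0.75, rounded up to 47, per arm.

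**7. Expected precision (ρ = 0.5).** The 95% CI half-width is t·k·√(2/n), with k = √(1−0.25) = 0.866 for ANCOVA and k = √(2×0.5) = 1 for change.
- n = 35: 0.41 (ANCOVA) to 0.48 SD (change).
- n = 26: 0.48 (ANCOVA) to 0.56 SD (change).

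**The case against.** The strongest reply is that this is a pilot. Feasibility, usability and acceptability are primary, efficacy is labelled preliminary, the same section concedes that the sample is small but suited to developmental research, and fully powered work is left to a later trial. That stands, and it confines the point to the secondary aim. It does not rescue the power statement, because the planned analyses it covers include the efficacy tests.

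Four stronger readings are tempting, but the document does not support them:

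- **That d was certainly used as f.** Step 4 shows another route to the same numbers. The very high correlation it needs is unsupported, but with no ρ stated the mix-up is an inference, not a demonstrated fact. Taking f = d/2 at ρ = 0.5 does give 35 per arm for d = 0.34, but then 10 per arm matches nothing and d = 0.17 needs 137.
- **That 11-37% is the true power.** It rests on ρ = 0.5, and ρ from 0.3 to 0.7 widens it to about 9-50%. It also leaves out adjustment for demographics, clustering within the peer-led groups and the coarse score for opioid misuse, which sums three yes/no items.
- **That 26 retained per arm breaches the plan's minimum of 30.** That minimum is given for the feasibility evaluation and is not said to mean week-12 completers. Feasibility data accrue throughout the 12 weeks, and retention is itself measured.
- **That weak efficacy tests would misdirect the decision on a full trial.** The document has no p-value rule for proceeding; the abstract's conclusions make the next step depend on feasibility.

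**Conclusion.** The point holds for the secondary efficacy aim. As written, 10 to 35 per arm does not follow from d = 0.17 to 0.34 at conventional settings, and the claim of adequate power is unsupported. Across correlations of 0.3 to 0.7, 35 per arm gives at best about 50% power at the most favourable end of the plan's own effect range and at most about 17% at the other end, before dropout. These figures assume two-sided 0.05 and a standardised difference at week 12 equal to the quoted d. The sample of 70, the allocation, the primary outcomes and the feasibility rationale are unaffected. This should be corrected, but it is not a flaw that threatens the trial.

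**What to change.** Keep 70 participants and justify the number on feasibility. In Power Analysis, delete or correct the 10 to 35 per arm and the statement of adequate power. In their place:

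- state the assumed alpha and pre-post correlation, with a range for the latter, and the resulting power as an illustration under those assumptions (steps 5 and 6);
- state that about 26 to 32 per arm are expected at week 12 under the cited retention;
- give the expected 95% CI half-width from step 7 for full and for 75% retention.

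In Anticipated Findings, replace the expectation of significant efficacy with a plan to report secondary outcomes as estimates with confidence intervals. If the G*Power input and output files still exist, checking whether f or d was entered would settle the origin of the figures.

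The cost is wording only and a less favourable stated power. No extra participants are needed. The Results section places ethics submission for the trial phase in early 2027 and recruitment in late 2027, so there is time on that schedule.

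### The stated 10 to 35 per arm and the adequate-power claim do not follow from Cohen d of 0.17 to 0.34; most plausibly d was entered into G*Power as f

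*Protocol article*

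**What the plan says.** The Power Analysis section of the protocol article first addresses feasibility, the primary aim, and cites pilot guidance of at least 30 per group. It then turns to preliminary efficacy, a secondary aim. From a review of digital interventions it "found small-to-medium effect sizes (Cohen *d*=–0.17 to –0.34) with a 6-month follow-up assessment"). It reports that "G-power analysis [112] estimated a sample size of 10 to 35 per arm for an RCT (repeated measures analysis of covariance"). After citing retention of 75% to 93% in earlier trials, it concludes that "a sample of 70 appears to be feasible and provides adequate power for proposed analytic plans".

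The analysis being powered is given under Multivariate Analyses: "Preliminary outcomes from baseline and 12 week will be tested using repeated measures analysis of covariance, controlling for demographics". Aim 3 fixes two arms of 35, allocated 1:1. The Power Analysis section ends by calling the small sample suitable for developmental research. The Anticipated Findings section nevertheless expects significant preliminary efficacy.

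**The concern.** Ten participants per arm is far too few to detect a standardised difference of 0.34 in any ordinary two-arm comparison, and 35 per arm is far too few for 0.17. A range this small suggests that the effect size was entered on the wrong scale. G*Power's repeated-measures F tests take Cohen f, whereas the section quotes Cohen d.

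Two things are at stake. The first is how the efficacy results will be read: if 70 is described as adequately powered, a non-significant result may be taken as evidence of no effect. The second is the large-scale trial that the pilot is meant to support. If the same calculation were reused there, 35 per arm would stand where 545 is needed at correlation 0.5, about 16 times as many (545/35 = 15.6).

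**Working it through.** **Inputs from the article.** d = 0.17 to 0.34 in absolute value, the stated 10 to 35 per arm and retention of 75% to 93% (Power Analysis); two measurements, baseline and 12 weeks (Multivariate Analyses); 35 per arm (Aim 3).

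**Inputs assumed, because the article gives none.** Alpha 0.05, target power 0.80, and baseline to 12-week correlation ρ of 0.5, varied below.

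**Formula.** For G*Power's repeated-measures within-between interaction with two groups and m = 2 measurements, the test is a noncentral F with λ = f² · N · m / (1 − ρ), df1 = 1, df2 = N − 2, where N is the total sample.

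**Step 1: reproduce the stated range with d entered as f, ρ = 0.5.**
- f = 0.34, N = 20: λ = 0.1156 × 20 × 2 / 0.5 = 9.25, power 0.82. N = 18 gives 0.77. Result: 10 per arm.
- f = 0.17, N = 70: λ = 0.0289 × 70 × 2 / 0.5 = 8.09, power 0.801. N = 68 gives 0.789. Result: 35 per arm.

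Both ends match exactly.

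**Step 2: convert d to f for this design.** Suppose the arms are equal at baseline and differ by d standard deviations at follow-up. The interaction component in each of the four cells is then ±d/4, so f = d/4. With N = 2n this gives λ = d² · n / (4(1 − ρ)), which is the ordinary two-sample test on change scores.
- d = 0.34, f = 0.085: N = 274 (power 0.801), 137 per arm.
- d = 0.17, f = 0.0425: N = 1090 (power 0.801), 545 per arm.

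**Step 3: what else could give 10 and 35?** With f = d/4 the pair appears at ρ of about 0.969. With f = d/2, the conversion for a simple two-group comparison, it appears at ρ = 0.875; at ρ = 0.5 that conversion gives 35 and 137.

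**Step 4: power at 35 per arm, all 70 analysed.** The group-by-time test uses λ = d² · 35 / (4(1 − ρ)). With baseline as a covariate, λ = (d² · 35 / 2) / (1 − ρ²). Each cell shows power for d = 0.17 and for d = 0.34.

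| ρ | Group-by-time | Baseline as covariate |
|---|---|---|
| 0.3 | 9% and 22% | 11% and 31% |
| 0.5 | 11% and 29% | 13% and 37% |
| 0.7 | 15% and 44% | 17% and 50% |
| 0.8 | 20% and 60% | 22% and 65% |

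Reaching 80% at d = 0.34 needs ρ of about 0.87 under either analysis. At that ρ, power for d = 0.17 is still only 28% to 30%; reaching 80% there needs ρ of about 0.97.

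**Step 5: detectable effect.** At ρ = 0.5 and 35 per arm, 80% power is reached at d = 0.68 (group-by-time) or d = 0.59 (baseline as covariate).

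**Step 6: attrition.** 75% of 35 is about 26 per arm and 93% is about 32. At ρ = 0.5 on the group-by-time test, 26 per arm gives about 9% and 23%, and 32 per arm gives 10% and 27%. The chosen 35 equals the top of the stated range, so it holds no allowance for loss.

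**The case against.** The strongest reply has four parts.

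*The cause is not proven.* A reader might infer that the range can only have come from entering d as f. The article does not support that: it gives no alpha, power, correlation or conversion, and Step 3 shows other routes to the same pair. This objection stands, and the cause is offered as the most plausible one. The alternatives do not rescue the figure, however. The d/2 route uses the wrong f for an effect that appears only at follow-up. The d/4 route needs a near-perfect correlation between self-reports taken before and after an intervention meant to change them.

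*Power depends on the unstated correlation.* This also stands. A single figure of 11% to 29% would be one row of the table. Nor can one say that a non-significant result is always the likelier outcome: at d = 0.34 and ρ = 0.8, power exceeds one half.

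*The trial size does not rest on this calculation.* A reader might infer that 35 per arm was adopted from G*Power. The section does not say so. It puts feasibility first with at least 30 per group, which 35 satisfies, and treats efficacy as secondary. No design feature or primary outcome changes.

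*It is a pilot, described as developmental, and the article reserves full power for a later trial.* That is fair context, but it does not withdraw the explicit statement that the sample "provides adequate power for proposed analytic plans". Those plans include the efficacy analysis.

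The missing alpha, power and correlation are not themselves a fault in a condensed article. The fault is that the effect sizes, the sample sizes and the conclusion, all printed together, do not fit.

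**Conclusion.** The point holds for the secondary efficacy aim. Neither 10 to 35 per arm nor the adequate-power statement follows from the quoted d, unless the baseline to 12-week correlation is close to 0.97. Over correlations of 0.3 to 0.8, with no dropout, 35 per arm gives 9% to 22% power at d = 0.17 and 22% to 65% at d = 0.34, taking both analyses together except that the low ends come from the group-by-time test. Attrition at the cited rates lowers this further.

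These figures assume two-sided alpha 0.05, equal baselines, an effect present only at follow-up and a continuous outcome. They do not show that the trial is too small for its primary purpose, and the article gives no ground for that reading.

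**What to change.** Keep 70 participants and justify the number on the feasibility aim and its minimum of 30 per group. Remove the 10 to 35 per arm range, or recompute it with d converted correctly and the assumed inputs stated. Replace the adequate-power wording with the actual power as a range over the assumed correlation, after allowing for attrition, and add that at correlation 0.5 the trial can detect only a d of about 0.6 to 0.7 with 80% power. Do not carry the 10 to 35 calculation into the proposal for the large-scale trial.

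The cost is one rewritten paragraph and a less favourable stated figure, with no extra participants. The article plans ethics submission of the Aim 3 protocol for early 2027, so the correction can be made in that document.

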### Project Timeline

A detailed study timeline is shown in Table 1.

**Table 1 table1:** The project timeline.

		Year 1	Year 2	Year 3	Year 4	Year 5
**Phase 1: formative study (aim 1)**		✓	✓			
	Literature review and assessment development (ie, surveys and semistructured interviews)	✓				
	IRB^a^ submission	✓				
	Peer leader recruitment, participant recruitment and assessment, and community advisory board establishment	✓				
	Transcription and data analysis or extraction		✓			
**Phase 2: intervention development (aim 2)**			✓	✓		
	Development of multimedia files or features based on data from formative research		✓			
	Establishment of IMB^b^-based intervention module packages		✓	✓		
	Development of prototype for social media groups and pages (ie, Instagram [Meta Platforms, Inc])			✓		
	Peer leaders’ and administrators’ training (doctoral clinical psychology trainees)			✓		
**Phase 3: intervention feasibility and preliminary efficacy evaluation study (aim 3)**				✓	✓	
	Participant recruitment, preintervention assessment, and randomized controlled trial assignment			✓		
	Delivery of intervention			✓		
	EMA^c^ surveys and paradata collection			✓		
	Postintervention assessment and interviews				✓	
	Data analysis				✓	
	Revisions based on participants’ feedback				✓	
	Dissemination and disclosure of research findings				✓	✓
	Preparation and submission a research proposal for a large-scale intervention effectiveness evaluation with a randomized controlled trial design				✓	✓

^a^IRB: institutional review board.

^b^IMB: information-motivation-behavioral skills.

^c^EMA: ecological momentary assessment.

### Ethical Considerations

All data (ie, qualitative and quantitative) and materials (including video, images, and comments) collected or generated in the proposed study are deidentified and stored on a password-protected drive to ensure confidentiality. Intervention materials will be only delivered in private Instagram groups, which are not accessible to public users. Before their participation, all participants are provided with informed consent that explains the study’s purposes, voluntary nature, and confidentiality. Participants are allowed to withdraw from the study at any time. Participants will receive e-gift cards for the completion of formative interviews (US $50) and each intervention assessment (preintervention and postintervention; US $30 each). The prorated incentive will be given according to the completion of EMA during the intervention period (eg, US $25 e-gift card for a 100% completion; US $15 for a 67% completion). Biweekly random prize draws of US $25 gift cards for these who post, attend meetings, and reply on the panels. At the end of the intervention, US $60 e-gift cards will be provided to participants who complete 90% of tasks during the intervention.

As a multiphase study, the protocol is reviewed by the research ethics boards in a sequential manner. A protocol for a formative interview study (aim 1) has been submitted to relevant institutional boards for review. Detailed information on the ethical approval and recruitment progress is provided in the subsequent sections. The protocol has been developed and reviewed in accordance with the SPIRIT (Standard Protocol Items: Recommendations for Intervention Trials checklist; Multimedia Appendix 1). The protocol of the formative study (aim 1) has been approved by the Institutional Review Board for Human Research at the University of South Carolina (#Pro00135306).

